##### Data Collection and Sources of Information

Most of the data will be collected from EMRs, such as socio-demographic variables and scores on the different scales. Other sources of information will be direct observation, interviews with patients and caregivers, and exchange of information with other HCNs involved, such as HCNs from social services or other healthcare facilities.

To promote participant retention and complete follow-up, monthly sessions will be held to assess the progress of this study. During these sessions, the study’s advancement will be discussed, and any concerns or deviations from the intervention protocol will be addressed.

Study data will be collected and managed using REDCap electronic data-capture tools hosted at Camp de Tarragona of the Catalan Institute of Health [25,26]. REDCap (Research Electronic Data Capture) is a secure, web-based software platform designed to support data capture for research studies, providing (1) an intuitive interface for validated data capture; (2) audit trails for tracking data manipulation and export procedures; (3) automated export procedures for seamless data downloads to common statistical packages; and (4) procedures for data integration and interoperability with external sources.

##### Data Analysis

Continuum variables will be described using means and standard deviations if they follow a normal distribution or using means and interquartile ranges otherwise. The normality of the variables will be described using the Kolmogorov test. Categorical variables will be described with percentages and 95% confidence intervals.

Outcomes will be compared between groups using the Chi-square test. A multivariate analysis (Cox regression) will be performed, introducing adjustment variables into the model: socio-demographic variables, risk areas, and covariates, as mentioned before. Covariate selection will be based on clinical relevance and statistical significance (*p* < 0.05 in univariate analysis or established predictors from previous research). The time until the event of the main outcome variables will be considered in the model.

For the “quality of life” outcome, the test scores (averages and percentiles) will be compared between the control and intervention groups at the beginning and at the end of the intervention using the *t* test.

Missing data will be handled under the principle of the worst-case scenario. However, different imputation strategies may be considered depending on the context.

The statistical package R (R foundation for statistical computing, Vienna, Austria; version 4.1.2 or later) will be used for all analyses. Statistical significance shall be established at *p* < 0.05.

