##### Sample Size

The expected effect size is a 10% reduction in hospital admissions, based on the baseline hospital admission rate of 65.89% in 2024 for the home care program at primary care centers in Tarragona, which belong to the Catalan Health Institute. We assumed a 95% confidence level (alpha error of 5%) and a statistical power of 80%. Additionally, a 15% loss to follow-up was factored into the calculation. With these assumptions, a total of 272 patients per group (control and intervention) will be required. The ARCSINUS approximation (GRANMO Sample Size Calculator v.8.0, available at www.datarus.eu/aplicaciones/granmo/) was used.

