##### Variables

The main outcome variables of this study are as follows:The proportion of patients with hospital admissions and avoidable hospital emergency visits (main variable) during the follow-up period.The percentage of patients with ulcers and falls.The total number of avoidable admissions and hospital emergency visits during the follow-up period.The total number of deaths and definitive institutionalizations.Quality of life, measured using the EuroQol-5D index, a record currently available in EMRs [22].

The following are considered as covariates:Age, sex, and socio-economic level [23] and the home care model.Main comorbidities, following the Charlson comorbidity index [24].

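### The main comparison is an unadjusted Chi-square and no named covariate is pre-entry hospital admission, which forgoes precision when only 10 centres face 10

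*Protocol article*

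**What the plan says.** All references are to the protocol article, Phase 2.

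- **Data Analysis** gives the between-group test for the outcomes: "Outcomes will be compared between groups using the Chi-square test". A multivariable Cox model follows. It adjusts for socio-demographic variables, risk areas and the listed covariates, chosen by clinical relevance and by univariate significance or known predictive value.
- **Variables** lists the covariates as "Age, sex, and socio-economic level [23] and the home care model", plus comorbidity by the Charlson index. Neither the patient's earlier admissions nor the centre's earlier admission rate appears. The main variable combines hospital admissions with avoidable emergency visits.
- **Sample Size** is "based on the baseline hospital admission rate of 65.89% in 2024 for the home care program at primary care centers in Tarragona". This is one pooled figure, for admissions only.
- **Data Collection and Sources of Information** takes most data from the electronic medical record (EMR).
- The **Phase 2 design paragraph** randomises 20 centres 1:1 and states no stratification or matching. The **Discussion** answers possible differences between groups by choosing similar centres and comparing baseline characteristics descriptively.

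**The concern.** A patient's recent admission history is usually informative about later admission, and centres may differ in how readily they admit. With 10 centres per arm, centres with higher usual admission can fall unevenly between arms by chance. An unadjusted comparison carries that difference into the estimated effect of the map, where it can look like an effect or mask one. A descriptive baseline table would show such an imbalance but would not take it out of the estimate.

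The stakes are precision and the credibility of this one allocation. The trial is open-label, and the Cox selection rule leaves the choice of terms partly to the data. Naming this covariate in advance therefore also removes a choice that would otherwise be made after the data are seen.

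**Working it through.** **Inputs from the protocol.** Control proportion 0.6589. "The expected effect size is a 10% reduction in hospital admissions", read here as 10 points, so 0.5589; the text does not say whether the reduction is absolute or relative. The section states "a 95% confidence level (alpha error of 5%) and a statistical power of 80"%, taken as two-sided. 272 per group with 15% loss gives 272 × 0.85 = 231 analysed. 20 centres at 1:1 gives 10 per arm and 231/10 = 23.1 analysed patients per centre.

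**Assumptions (not in the protocol).** The correlation between pre-entry and follow-up admission, written ρ without clustering, and rw (patient level) and rb (centre level) with clustering; and an ICC of 0.02 or 0.05.

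**The plan's own figure.** The arcsine formula, n = 2(1.960 + 0.842)² / (2·asin√0.6589 − 2·asin√0.5589)², gives 373 evaluable and 373/0.85 = 439 per group. A 10% relative reduction (to 0.5930) gives 845 and 995. The stated 272 is not reproduced. That is a separate and larger problem; here 272 is taken as given.

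**Variance.** v = (0.6589 × 0.3411 + 0.5589 × 0.4411)/2 = (0.2248 + 0.2465)/2 = 0.2356.

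**Step 1: no clustering.** SE² = (2v/231)(1 − ρ²); power = Φ(0.10/SE − 1.96).

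| ρ | variance cut | SE | power |
|---|---|---|---|
| 0 | 0% | 0.0452 | 60.0% |
| 0.2 | 4% | 0.0443 | 61.8% |
| 0.3 | 9% | 0.0431 | 64.1% |
| 0.4 | 16% | 0.0414 | 67.6% |
| 0.5 | 25% | 0.0391 | 72.5% |

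The gain over no adjustment is 1.8 to 12.5 points.

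**Step 2: with clustering.** SE² = (2v/231)[(1 − ICC)(1 − rw²) + 23.1 × ICC × (1 − rb²)]. Power is from the non-central t with 18 degrees of freedom unadjusted, and 17 once a centre-level term is fitted.

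| ICC | rw, rb | SE | power |
|---|---|---|---|
| 0.02 | none | 0.0542 | 41.5% |
| 0.02 | 0.2, 0.5 | 0.0512 | 45.3% |
| 0.02 | 0.3, 0.5 | 0.0503 | 46.7% |
| 0.02 | 0.3, 0.7 | 0.0480 | 50.3% |
| 0.05 | none | 0.0655 | 30.4% |
| 0.05 | 0.2, 0.5 | 0.0602 | 34.7% |
| 0.05 | 0.3, 0.5 | 0.0594 | 35.5% |
| 0.05 | 0.3, 0.7 | 0.0545 | 41.0% |

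The gain is about 4 to 11 points. These figures describe an analysis that accounts for centre. They are not the power of the planned patient-level Chi-square, which ignores centre.

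**Step 3: chance difference between arms in true centre rates.** SD = √(2 × ICC × v / 10). At ICC 0.02: √(2 × 0.02 × 0.2356/10) = 0.031. At ICC 0.05: √(2 × 0.05 × 0.2356/10) = 0.049. That is 3.1 to 4.9 points against a 10-point target.

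**The case against.** The strongest reply is that the plan is not without adjustment. The Cox model covers the main outcome and is nowhere called secondary. It adjusts for risk areas drawn from the medical record as well as the listed covariates, and its rule admits established predictors, which could include prior admission. This stands in part: the adjusted analysis is open to the covariate. But it makes no commitment, and nothing in that rule reaches the Chi-square.

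It is also fair that the gains above are measured against no adjustment at all. Beyond age, Charlson and risk areas the added gain would be smaller wherever these carry the same information, and choosing similar centres could lower the ICC.

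A condensed article may leave covariate detail to an analysis plan. This one, however, chooses the test and names the covariates, so the comment concerns a stated choice.

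Three stronger readings are tempting and are not supported:

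- *The baseline value of the main outcome is already in hand.* The protocol prints a single pooled rate, which cannot adjust anything. It covers admissions only, while the main variable also counts avoidable emergency visits. Patient-level or centre-level values are plausible from the EMR, but the protocol does not say they are held.
- *The comparison is biased.* Chance imbalance under randomisation is not bias; a standard error that respects centre allows for it. The planned Chi-square does not, which is the separate clustering defect.
- *Adjustment would rescue the trial's power.* No scenario examined reaches 80%.

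**Conclusion.** The point holds as an improvement to a stated analysis choice, not as an error that invalidates the trial. The Chi-square and the named covariates omit pre-entry admission although the programme records admissions, and the remaining safeguards (an open Cox rule, similar centres, a descriptive table) do not ensure that it is used.

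The size is moderate and uncertain. At weak correlations the benefit is small: about 2 points of power without clustering at ρ = 0.2, and about 4 points with clustering at rw = 0.2 and rb = 0.5. All of it depends on correlations and an ICC that the protocol does not give, and on reading the 10% reduction as percentage points. The sample size and the neglect of clustering matter more and have to be resolved in their own right.

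**What to change.** **Variables.** Add, from the EMR, the patient's hospital admission in the 12 months before entry and, if obtainable, avoidable emergency visits in the same period. Where available, add the centre's 2024 home care admission proportion.

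**Data Analysis.** Make the main comparison a regression of the main proportion that

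- always includes these terms, whatever their univariate p-value; and
- accounts for centre, by a random effect or a cluster-level analysis with small-sample degrees of freedom.

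The second element is essential: a regression with the added covariates but nothing for centre would still ignore clustering, and the clustered figures above would not apply. Put the same terms in the Cox model and keep the Chi-square as description only. If a risk difference is wanted, state that the model will report it as a marginal quantity.

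**Cost.** One added EMR extraction, revised wording, and one centre-level degree of freedom (18 to 17, already counted above). No extra patients or visits.

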#### 2.3.2. Phase 2: Cluster-Randomized Clinical Trial Across Different Primary Care Centers in Countryside of Tarragona, Spain

A cluster-randomized clinical trial will be carried out for 12 months. The study will be conducted in 20 primary care centers in the Tarragona area. These centers will be randomly allocated into two groups at a ratio of 1:1. The intervention group will have the home care visual map available. No blinding will be implemented in this study. This open-label design is chosen due to the nature of the interventions, which will make blinding unfeasible

This phase of this study will follow the SPIRIT Statement guidelines for reporting clinical trial protocols.

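### Centres are randomised, but the named Chi-square, Cox and t tests treat patients as independent, so p-values are too small and the type I error exceeds 5% under any appreciable within-centre correlation

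*Protocol article*

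**What the plan says.** Section 2.3.2 of the protocol article makes the centre the unit of randomisation: "The study will be conducted in 20 primary care centers in the Tarragona area", and "These centers will be randomly allocated into two groups at a ratio of 1:1". That is 10 centres per arm, followed for 12 months.

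The Data Analysis section of the same phase then names the tests: "Outcomes will be compared between groups using the Chi-square test. A multivariate analysis (Cox regression) will be performed". Quality of life is compared by t test. The decision rule is "Statistical significance shall be established at *p* < 0.05".

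The Cox adjustment set consists of socio-demographic variables, risk areas and the covariates listed under Variables: age, sex, socio-economic level, home care model and the Charlson index. Centre is not among them. Nowhere does the article mention an ICC, a centre random effect, frailty, GEE, cluster-robust variance or a centre-level analysis.

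The outcomes under Variables include patient proportions and also totals, for example "The total number of avoidable admissions and hospital emergency visits during the follow-up period".

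**The concern.** A test that treats patients as independent matches a trial that randomises patients. Here whole centres are allocated, and the map acts through the professionals of each centre. Differences between centres in staff and referral habits feed directly into the difference between arms. With 10 centres per arm, that variation does not average out however many patients each centre recruits. A centre-level comparison has only 20 − 2 = 18 degrees of freedom.

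The error favours a false claim. Standard errors come out too small, intervals too narrow, and a conclusion that the map reduces admissions is reached by chance more often than the 5% the protocol promises. The main variable is directly affected.

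A second, smaller mismatch lies in the same sentence. It assigns the Chi-square test to the outcomes generally, and a separate comparison is named only for quality of life. Event totals, to which one patient can contribute several events, therefore fall under a test that needs independent counts.

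**Working it through.** **Inputs from the protocol article.** 20 centres, 1:1 (section 2.3.2); 272 patients per group, 15% loss, baseline admission rate 65.89%, a 10% reduction, alpha 5%, power 80% (Sample Size); significance at 0.05 (Data Analysis).

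**Assumed.** The ICC is not given, so a range is shown. Tests are taken as two-sided and centres as equal in size.

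**The plan's own figure.** The stated 272 per group does not reproduce. The arcsine formula is n = 2·[(1.96 + 0.842)/h]², with h = 2·asin√p₁ − 2·asin√p₂. For 65.89% against 55.89%, h = 0.2053 and n = 373, or 373/0.85 = 439 with loss. A relative 10% reduction (to 59.30%) gives about 995 with loss. That is a separate problem. Here 272 is used only to obtain the number of patients per centre.

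**Patients per centre.** Enrolled: 272/10 = 27.2. Evaluable after loss: 272 × 0.85/10 = 23.1.

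**Formulas.** Design effect DE = 1 + (m − 1)·ICC. Real type I error of a nominal 5% test that ignores clustering = 2·[1 − Φ(1.96/√DE)].

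Example, m = 23.1 and ICC 0.02: DE = 1 + 22.1 × 0.02 = 1.44; 1.96/√1.44 = 1.63; error = 10.3%.

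| ICC (assumed) | DE, m = 23.1 | Type I error | DE, m = 27.2 | Type I error |
|---|---|---|---|---|
| 0 | 1.00 | 5.0% | 1.00 | 5.0% |
| 0.005 | 1.11 | 6.3% | 1.13 | 6.5% |
| 0.01 | 1.22 | 7.6% | 1.26 | 8.1% |
| 0.02 | 1.44 | 10.3% | 1.52 | 11.2% |
| 0.03 | 1.66 | 12.9% | 1.79 | 14.2% |
| 0.05 | 2.11 | 17.7% | 2.31 | 19.7% |
| 0.10 | 3.21 | 27.4% | 3.62 | 30.3% |

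**Simulation.** Beta-binomial data, 20 centres, true rate 65.89% in both arms, 100,000 runs per setting:

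| ICC | Chi-square, 23 per centre | Chi-square, 27 per centre | Yates-corrected, 27 per centre |
|---|---|---|---|
| 0 | 5.0% | 5.1% | 4.1% |
| 0.01 | 7.7% | 8.3% | 6.9% |
| 0.02 | 10.3% | 11.2% | 9.6% |
| 0.05 | 17.7% | 19.8% | 17.8% |
| 0.10 | 27.4% | 30.5% | 28.2% |

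A t test on the 20 centre proportions (18 degrees of freedom) stayed between 4.9% and 5.1% in every setting.

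**Event totals.** If repeated events make the variance k times the mean, treating events as independent gives an error of 2·[1 − Φ(1.96/√k)]. This is 11% at k = 1.5, 17% at k = 2 and 26% at k = 3, before any clustering by centre. The values of k are assumptions.

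**Power under a valid test.** Approximately Φ(h·√(n/2) − 1.96), with h = 0.2053 for a 10-point reduction and n the effective number per arm, 231.2/DE. Without clustering this is 60%. At ICC 0.01, 0.02 and 0.05 the effective n is 189, 160 and 110, and power is about 52%, 45% and 33%.

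**The case against.** - **The ICC is unknown.** This stands as a limit on the size. At ICC 0 there is no inflation, and at 0.005 it is about 6.5% with 27.2 per centre. But the protocol gives no reason to expect an ICC of zero, and the choice of a cluster design itself anticipates that a centre's patients share their care.
- **Similar centres will be selected, and the Cox model adjusts for home care model and socio-economic level.** Both may lower the residual correlation. Neither makes patients within a centre independent, and the Chi-square and t tests are not adjusted at all.
- **The figures use the uncorrected Chi-square test.** The protocol does not say which version applies. The Yates correction lowers the error by about one to two points, but it remains above 5% at every ICC of 0.01 or more.
- **An article condenses, so a frailty term or robust variance could be set out elsewhere.** This has some force for the Cox model, which was not simulated; for it and for the t test, only the general variance argument applies. It has little force for the Chi-square and t tests, which are named outright. An analysis plan that follows this text would be wrong, and one that does not would contradict it.
- **The text does not explicitly link the Chi-square test to event totals.** True, and the 17% depends on an assumed overdispersion. The literal reading still leads there, because only quality of life receives another group comparison. This point is secondary, and the main conclusion does not depend on it.

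**Conclusion.** The concern holds and must be fixed. The protocol states an analysis that does not fit its own randomisation; this is not a detail left for later. For ICCs of 0.01 to 0.05 and 23 to 27 patients per centre, the real type I error of the primary Chi-square comparison is about 8% to 20% against a nominal 5%, and true standard errors are 1.1 to 1.5 times those reported. The direction is certain for any positive ICC. The size rests on the assumed ICC and on equal centre sizes; unequal sizes would make it worse. The event-total mismatch needs correcting in the same revision.

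**What to change.** Rewrite the Data Analysis section before any outcome data are seen:

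1. **Main variable.** Name one primary test that accounts for centre: a mixed logistic or GEE model with centre as the cluster and a small-sample correction, or a t test on the 20 centre proportions with 18 degrees of freedom. Report the risk difference with its interval, and the ICC.
2. **Time to first event.** Cox model with shared centre frailty, or a cluster-robust variance with a small-sample correction.
3. **Event totals.** Negative binomial model with a person-time offset and a centre effect.
4. **EuroQol-5D.** Linear mixed model with a random centre effect.

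The essential requirement is that every comparison accounts for centre and for there being only 20 clusters. Equivalent methods would do.

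The direct cost is protocol and analysis-plan wording and somewhat more programming in R; no extra data items are needed. Intervals will be wider. The indirect cost is that valid tests have less power than the plan implies: roughly 45% for a 10-point reduction at ICC 0.02 with the present 272 per group. The sample size should therefore be recalculated with a stated ICC and design effect in the same revision.

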The population that is elderly and frail, or at risk of becoming so, need advice focused on their circumstances from HCNs with the aim of preserving their autonomy, improving their quality of life, avoiding AEs, and reducing mental and physical deterioration. By identifying certain factors, proactive actions could be taken to prevent or reduce frailty and improve health and quality of life [9,19]. In Germany, an intervention based on nurse and physician training and the use of a software tool aimed to reduce adverse drug events in home care patients [20]. In Canada, integrative software was used to support person-centered care, clinical and management processes, and proactive care in the home care environment [21].

Despite the availability of extensive patient information in medical records, covering risk areas such as falls, infections, medication safety, caregiver support, autonomy, symptom control, and social determinants, this information remains fragmented across different records. This fragmentation hinders HCNs from quickly identifying critical health concerns and prioritizing patient safety. However, there is a notable gap in the literature regarding the use of information and communication technologies to streamline patient risk identification in home care settings.

To address this issue, the present study leverages information and communication technologies to develop a visual alert map that consolidates key patient data. By translating medical records into an accessible format, this tool aims to enhance HCN practices, facilitate prioritization, and reduce AEs in home care.

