#### 2.3.1. Phase 1: Design of Home Care Visual Map

The first phase consists of designing a tool based on a visual map available in the EMRs of home care patients.

In this way, the professionals who attend to home care patients will have immediate access to the visual map including the main health areas related to each patient. This phase includes two sub-phases: the identification of health areas and their contributing factors.

Identification of health areas and their contributing factors

First, a group of experts specializing in home care programs and chronic health conditions will be formed. This group will search and discuss the variables available in EMRs that can act as risk factors and classify them into different health areas.

The selection of the variables will be based on data analysis, discussion, and consensus among the experts. The agreed health areas will constitute the visual map. An example of a visual map with health areas and their contributing factors is shown in Figure 2.

2.Risk weighting with a group of experts

Once the health areas and their contributing factors are identified, the risk or problem per area will be weighted as follows: no risk (in green), potential risk (in orange), and current problem (in red). This weighting will be take into account the magnitude or severity of the measured problem. An example of the visual map with risk weighting is shown in Figure 3.

The research team will form a group of experts for each area and the cut-off points will be decided to classify the risk.

Finally, all this information will be registered and integrated into EMRs.

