The visual map will enable healthcare professionals to determine appropriate actions based on the color-coded health areas, whether by implementing health promotion activities, undertaking preventive measures, or addressing existing issues requiring intensive intervention. Moreover, having a standardized visual map for all healthcare professionals will ensure continuity in care and enhance the monitoring of home care patient performance [34].

Despite its advantages, the visual map will have some limitations, including potential technological complexities in implementing EMRs. These challenges may involve integration with existing systems, data accuracy, and the adaptation of the tool to the specific needs of various healthcare settings. Moreover, organizational barriers, such as workflow disruptions and resistance from healthcare professionals, may also affect the tool’s adoption. However, the research team has extensive experience in innovation and the implementation of various technological tools in the field of quality and patient safety [35,36]. In fact, some of these innovations have been successfully scaled up and integrated across the entire autonomous community. To further support the implementation of the visual map, a training session will be conducted at the start of this study, and monthly meetings will be held to monitor usage, address concerns, and provide ongoing support to professionals. This experience and structured support plan will help mitigate the challenges and facilitate the smooth adoption of the tool.

In phase 2 of this study, different socio-demographic and socio-economic characteristics of the patients enrolled could influence the results. To mitigate these differences, similar centers will be selected and a comparative descriptive baseline analysis between the control and intervention groups will be conducted. This approach will help reduce potential bias and improve the robustness of the findings.

Incorporating phase 3 in this study will be crucial for gathering qualitative user feedback on the visual map to ensure that it fits well within the work environment and is intuitive to use. This adaptation aims to increase the use of the visual map in daily routines, ultimately leading to time savings for HCNs [37].

In conclusion, the visual map will enhance the safety of vulnerable patients in a less controllable environment, promoting patient safety, and aiding in resource management and distribution decision-making.

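### The adjusted Cox model is not fixed in advance: covariates may enter by univariate p < 0.05, and the map's own risk areas enter without being limited to baseline values

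*Protocol article*

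**What the plan says.** Section 2.3.2, Data Analysis, plans a Chi-square comparison between groups and then a multivariable Cox regression, "introducing adjustment variables into the model: socio-demographic variables, risk areas, and covariates, as mentioned before". The next sentence sets a selection rule: "Covariate selection will be based on clinical relevance and statistical significance", explained in brackets as p "< 0.05 in univariate analysis or established predictors from previous research".

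Section 2.3.2, Variables, already lists the covariates: "Age, sex, and socio-economic level [23] and the home care model", and "Main comorbidities, following the Charlson comorbidity index". Risk areas are not on that list.

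The article uses the term risk areas in the Introduction for information held in medical records, "covering risk areas such as falls, infections, medication safety, caregiver support, autonomy, symptom control, and social determinants". Section 2.3.1 says how the map presents its areas: "the risk or problem per area will be weighted as follows: no risk (in green), potential risk (in orange), and current problem (in red"). The Discussion says that the map supplies real-time information on the person's condition and lets professionals "determine appropriate actions based on the color-coded health areas". No section says when the risk areas entered in the Cox model are to be measured.

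**The concern.** There are two separate weaknesses, both in rules that the article itself states.

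**Selection by trial p-values.** In a randomised trial, covariates are adjusted for because they are known to be prognostic, and they can be named beforehand. Here one sentence enters all the listed covariates and the next makes entry depend in part on p-values from the trial's outcome data. The article does not say how clinical relevance, significance and prior evidence combine, or which variables count as established predictors. Hazard ratios are non-collapsible, so a different covariate set also means a different conditional hazard ratio as the target. With no blinding, a model settled after outcomes are seen is hard to defend.

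**Adjusting for what the map is meant to change.** If the map works, it does so by prompting action on the coloured areas. A risk-area status recorded after the map is in use is then a step on the path from allocation to outcome, and conditioning on it removes that part of the effect. Falls are both a risk area in the Introduction and an outcome in Variables, so a follow-up value could also overlap with an outcome. At stake is the only analysis that the article describes as covariate-adjusted and as using time to event.

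**Working it through.** The plan gives no figure on this point to reproduce. The calculations below are illustrations, with their assumptions stated.

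**1. How much can the p-value route vary?**

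Inputs from Sample Size: 272 per group, 15% loss, admission rate 65.89%, 10% reduction. The reduction is read here as percentage points (assumption), which gives 55.89%.

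- Chance that at least one of k purely null, independent candidates passes p < 0.05: 1 − 0.95^k. For k = 5 this is 23%, for k = 10 it is 40%, for k = 20 it is 64%.
- Expected events: 272 × 0.85 ≈ 231 per group, and 231 × (0.6589 + 0.5589) ≈ 281.
- Chance that a real, balanced binary predictor passes: Φ(√(281 × 0.25) × ln HR − 1.96), with √70.25 ≈ 8.38.
  - HR 1.2: Φ(8.38 × 0.182 − 1.96) = Φ(−0.43) ≈ 33%
  - HR 1.3: Φ(8.38 × 0.262 − 1.96) = Φ(0.24) ≈ 59%
  - HR 1.5: ≈ 92%

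For any variable that depends on the p-value route, modest real predictors are often left out and null ones sometimes let in. These figures ignore clustering by centre.

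**2. What does the timing of the risk areas do?**

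- Hazard ratio implied by 65.89% against 55.89% under proportional hazards: ln(1 − 0.5589) / ln(1 − 0.6589) = ln(0.4411) / ln(0.3411) ≈ 0.76, so the log hazard ratio is about −0.273.
- Assumption: one risk-area score with log hazard ratio 0.5 per unit. The map lowers the follow-up score, and a share s of the total effect runs through that reduction.
- Adjusting for the follow-up score leaves only the direct part, 0.761^(1 − s). For s = 0.5 this is 0.761^0.5 ≈ 0.87; for s = 1 it is 1.00.

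A Cox simulation on the same assumptions (272 per arm, 300 replicates, no clustering) agrees:

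| Share through risk areas | Unadjusted HR | Adjusted for baseline score | Adjusted for follow-up score |
|---|---|---|---|
| none | 0.77 | 0.76 | 0.75 |
| half | 0.77 | 0.77 | 0.87 |
| all | 0.78 | 0.77 | 1.00 |

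The proportion of significant results falls from 69% with baseline adjustment to 23% with follow-up adjustment when the share is half, and from 65% to 4% when it is all. Baseline adjustment is harmless in every row, so the timing of measurement decides the matter.

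**The case against.** - **The p-value is not the only route.** This stands. Clinical relevance and established predictors also count, so recognised predictors such as age or comorbidity need not depend on trial p-values. A reader might count 2^5 = 32 possible models from the five listed covariates; the established-predictor clause does not support that count. What remains is that the set is partly data-dependent and nobody can write it down today.
- **Standard errors.** A reader might infer that screening makes the standard error of the treatment effect too small. Neither the article nor the check supports that. In a null simulation (272 per arm, five covariates independent of arm, no clustering, 4,000 replicates), the screened model had mean standard error 0.108 against an empirical standard deviation of 0.109 and type I error 5.5%. The fixed model gave 0.109, 0.110 and 5.7%. The objection to screening is lack of pre-specification, not a shown loss of validity.
- **The risk areas may be baseline values.** This is the strongest point. The article never says that updated values will be used, and the Discussion plans a baseline comparison of the groups. The underlying information sits in the medical record and can exist in both arms. Reading the model's risk areas as the map's coloured areas is an inference, though the Introduction and Section 2.3.1 support it well. The bias is therefore possible, not certain.
- **Too many terms.** A reader might multiply the seven areas in the Introduction by two contrasts each and set 14 parameters against 20 centres. That list is only of examples, the final areas are left to the Phase 1 experts, and for patient-level terms the number of patient events also matters. The comparison does not hold.
- **This belongs in an analysis plan that is not shown.** Finer detail could. But the article itself states the screening rule and names risk areas as adjustment variables, so these are choices made, not omissions.

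**Conclusion.** The concern holds in a limited form. The article's rule leaves the adjustment set, and so the conditional hazard ratio, partly dependent on the outcome data of an unblinded trial, when a suitable fixed list is already in Variables. It also admits risk areas without a time restriction. If follow-up values were used, the adjusted effect would be pulled towards no benefit: from 0.76 to 0.87 if half the effect runs through them and to 1.00 if all does. Those sizes rest on an assumed risk-score effect, an absolute reading of the 10% reduction, and no clustering; the mediated share is unknown, so the range matters rather than any single value. With baseline values the hazard ratio stays at about 0.76 to 0.77.

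A reader might conclude that the trial's main result will be biased. The article does not support that: the unadjusted Chi-square comparison is untouched, and the article does not say which analysis is primary. The point should be settled before outcome data are seen, because a later repair would not be credible in an open-label trial.

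**What to change.** In Section 2.3.2, Data Analysis:

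1. Delete the univariate p < 0.05 screen.
2. Pre-specify one adjusted Cox model with the covariates already listed in Variables (age, sex, socio-economic level, home care model, Charlson comorbidities), all measured at baseline and kept whatever their p-values.
3. Remove risk areas from the model that estimates the map's effect. Alternatively, restrict them to one value per patient, fixed before the map is switched on and derived by the same rules in both arms.

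The cost is mainly wording. If risk areas are kept, they must also be derived from the records of control patients at the same time point. The article says that most data come from the medical record, but not that every covariate does, so availability at baseline should be confirmed.
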